## Abstract

**Background:**

Most skin cancers are preventable by encouraging consistent use of sun protective behaviour. In Australia, adolescents have high levels of knowledge and awareness of the risks of skin cancer but exhibit significantly lower sun protection behaviours than adults. There is limited research aimed at understanding why people do or do not engage in sun protective behaviour, and an associated absence of theory-based interventions to improve sun safe behaviour. This paper presents the study protocol for a school-based intervention which aims to improve the sun safe behaviour of adolescents.

**Methods/design:**

Approximately 400 adolescents (aged 12-17 years) will be recruited through Queensland, Australia public and private schools and randomized to the intervention (n = 200) or 'wait-list' control group (n = 200). The intervention focuses on encouraging supportive sun protective attitudes and beliefs, fostering perceptions of normative support for sun protection behaviour, and increasing perceptions of control/self-efficacy over using sun protection. It will be delivered during three × one hour sessions over a three week period from a trained facilitator during class time. Data will be collected one week pre-intervention (Time 1), and at one week (Time 2) and four weeks (Time 3) post-intervention. Primary outcomes are intentions to sun protect and sun protection behaviour. Secondary outcomes include attitudes toward performing sun protective behaviours (i.e., attitudes), perceptions of normative support to sun protect (i.e., subjective norms, group norms, and image norms), and perceived control over performing sun protective behaviours (i.e., perceived behavioural control).

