#### Sample size

A total of 400 participants (200/group) is aimed to be recruited. Based on our previous research in the area [28], it is anticipated that there will be approximately 35% attrition over 4 weeks of follow-up for reasons such as school absence or failure to complete follow-up questionnaires. A total sample of approximately 260 (400-140) completing participants (130/group) is required to detect a medium effect in sun safety behaviour. This sample size was determined by power analysis using the G*Power program [29,30]. Significance level (alpha) was established at 0.05 to avoid a Type 1 error, power (1-beta) was set at 95% to avoid a Type II error, and effect size was determined at .25. Therefore, for a 95% chance of detecting as significant a 4 week difference in sun safe behaviour, approximately 130 participants in each group are needed to complete the study.

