#### Variables

Demographic data collected pre-intervention will include age (in years) and sex (male or female). Data will also be collected on colour of skin before tanning (very fair, fair, olive or brown, Asian, black), colour of skin with repeated exposure to the sun light without protection (go very brown and deeply tanned, get moderately tanned, get mildly or occasionally tanned, get no suntan at all or occasionally get freckled), natural hair colour (black, dark brown, light brown, dark blonde, light blonde, red), eye colour (dark brown, light brown, green, blue), and hours spent in the sun in the past week.

Primary outcome variables will assess the effectiveness of the intervention in improving students' sun protection intentions and behaviour. Secondary outcome variables will assess the effectiveness of the intervention as a means of improving students' attitudes toward performing sun protective behaviours (i.e., attitudes), perceptions of normative support to sun protect (i.e., subjective norms, group norms, and image norms), and perceived control over performing sun protective behaviours (i.e., perceived behavioural control) (Table 1).

**Table 1 T1:** Primary and Secondary Outcome Measures

Domain	Variable	Number of items	SCALE	MEASUREMENT STRATEGIES

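### Two unranked primary outcomes share one alpha of 0.05 and only behaviour is powered: the false-positive rate is about 7-10% if either outcome alone can support the claim.

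*Protocol article*

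**What the plan says.** The Abstract (Methods/design) gives two primary outcomes: "Primary outcomes are intentions to sun protect and sun protection behaviour". The Variables section does the same: "Primary outcome variables will assess the effectiveness of the intervention in improving students' sun protection intentions and behaviour". Table 1 lists both under the primary heading. None of the three places puts one outcome ahead of the other.

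The Sample size section gives the only significance level in the article: "Significance level (alpha) was established at 0.05 to avoid a Type 1 error". It belongs to a calculation for behaviour alone: "A total sample of approximately 260 (400-140) completing participants (130/group) is required to detect a medium effect in sun safety behaviour". The same section describes the aim as sizing "for a 95% chance of detecting as significant a 4 week difference in sun safe behaviour". Intention does not appear there.

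Data Analyses plans general linear models for each change outcome, with group, time and group-by-time effects. It does not say which term decides the primary question. The hypothesis at the end of the Background expects improvement in beliefs, intentions and behaviour, and gives no rule on how many of these must be significant.

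**The concern.** The choice of primary endpoint is core protocol content, and the article does address it: it names two outcomes of equal rank and sizes the trial for one. As worded, the plan allows the intervention to be called effective on intention alone, although the stated purpose is better sun protective behaviour and the power calculation concerns behaviour. The error rate of a claim that either outcome can support is not the 5% attached to one test. A reader of the results could not tell from the protocol which outcome was meant to decide.

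**Working it through.** **Inputs from the article.** Two primary outcomes (Abstract, Variables, Table 1). From Sample size: alpha 0.05; power ("power (1-beta) was set at 95% to avoid a Type II error"); effect size ("effect size was determined at .25"), called medium; attrition 35%; 260 completers.

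**Assumptions.** The article gives neither the correlation between the two test statistics nor the sidedness of the tests. I take two-sided tests and a correlation from 0 to 0.9. The effect-size metric is not named; I read .25 as Cohen's f. Read as a standardised mean difference d, it would need 416 per group, and 130 per group would give about 52% power, so that reading does not fit.

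**The plan's own figure.** Attrition: 400 × 0.35 = 140, and 400 − 140 = 260. Power comes from the noncentral F distribution with noncentrality N × f² = 260 × 0.0625 = 16.25, at alpha 0.05:

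| Test | Smallest N for 95% | Power at 260 |
|---|---|---|
| 1 df | 210 | 98.0% |
| 2 df | 251 | 95.7% |

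The 2-df test comes closer to the stated figure. On either reading, 260 completers support 95% power for one outcome at 0.05.

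**Error rate if either outcome suffices.** For independent tests: 1 − 0.95² = 0.0975. For correlated two-sided tests, the rate is 0.05 + 0.05 − P(both significant), from the bivariate normal distribution with no true effect on either outcome:

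| Correlation | P(both significant) | P(at least one significant) |
|---|---|---|
| 0 | 0.25% | 9.75% |
| 0.3 | 0.5% | 9.5% |
| 0.5 | 0.9% | 9.1% |
| 0.7 | 1.7% | 8.3% |
| 0.9 | 3.0% | 7.0% |

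One overall 2-df group-by-time test per outcome gives nearly the same: 9.8% at correlation 0, 9.1% at 0.5 and 8.4% at 0.7 (simulated). The inflation therefore comes from having two outcomes and does not depend on separate tests per visit.

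**Error rate if both must succeed.** With no effect on either outcome, it is the middle column above. If only one outcome is truly affected, the other must still pass its own 0.05 test. The rate therefore never exceeds 5%.

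**Power for behaviour if alpha is split 0.025/0.025** (f = 0.25):

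| Test | Smallest N for 95% | Power at 260 |
|---|---|---|
| 1 df | 245 | 96.2% |
| 2 df | 288 | 92.5% |

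**The case against.** The strongest reply is that a journal article condenses a fuller protocol, so the handling of multiplicity may sit in a document not shown. The 0.05 is an input to the sample size and is not stated as a testing rule for both outcomes. The aims and the hypothesis join intentions and behaviour with an *and*, which fits a rule that both must succeed at least as well as a rule that either will do. Sample size also already singles out the four-week behaviour contrast.

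Much of this stands. The inflation is conditional, and a missing adjustment method would not by itself be a finding in an article. What remains is that the article does state the primary endpoints, gives them equal rank, and powers only one. An *and* in an aim is not a success rule.

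A reader might go further and infer that each outcome is tested at 0.05 at both follow-ups, which gives 1 − 0.95⁴ = 18.5%. The article does not support this. Data Analyses describes a model per outcome and no separate test per visit. The 18.5% also needs four independent tests, although the measurements come from the same pupils; at correlations of 0.5 to 0.8, four such tests would give about 16% down to 12%.

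A reader might also infer that splitting alpha costs nothing. That is true for a 1-df test only. For the 2-df test, which lies closer to the plan's own 260, power falls below the stated 95%.

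**Conclusion.** The point holds in conditional form. If a significant result on either primary outcome can support the effectiveness claim, the false-positive rate is about 7-10% instead of 5%. This rests on two two-sided tests at 0.05 and a correlation between 0 and 0.9; the article gives no value. If both outcomes are required, the rate is at most 5% and there is no inflation, but the article does not limit the claim in that way. The mismatch between two equal primary outcomes and a sample size built on one of them is plain on the page and needs no assumption. It should be corrected, and this can be done without changing the size of the trial.

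**What to change.** - In the Abstract and in Variables (with Table 1), make sun protection behaviour at Time 3 the single primary endpoint, to match Sample size.
- In Data Analyses, name the model term or contrast that tests it.
- Test intention at Time 3 next, at 0.05, only if behaviour is significant. Label all Time 2 results secondary.
- Reconcile the definition of Time 3. The Abstract counts the one-week and four-week follow-ups as post-intervention, while Measurement counts them from the start of the intervention. With sessions spread over three weeks, the second definition puts the first follow-up inside the delivery period.

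The cost is wording only: behaviour keeps the full 0.05 and recruitment stays at 400. The downside is that intention cannot carry a confirmatory claim if behaviour fails.

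If both outcomes are to stay primary, either apply Holm's procedure to the two Time 3 tests or state that both must be significant. With an alpha split, 260 completers give behaviour 96.2% power for a 1-df test but 92.5% for a 2-df test; in the second case the stated 95% would need restating. For Holm these figures are minimums, because its second step uses 0.05. If both must succeed, joint power cannot exceed the lower of the two powers, and the article gives none for intention.

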**Discussion:**

The study will provide valuable information about the effectiveness of the intervention in improving the sun protective behaviour of adolescents.

## Background

Skin cancer is the most prevalent form of cancer in Australia, accounting for approximately 80% of all new cancers diagnosed annually [1,2]. For Australians, this translates into 380,000 treated cases of skin cancer per year [1,2]. The numbers of new cases of skin and lip cancers (excluding non-melanoma skin cancers) for Australian women are projected to increase by 27% in the year 2011 [1]. For Australian men, projected increases in skin and lip cancer cases are even higher at 32% [1]. Exposure of the skin to the sun is the most consistently implicated factor causing skin cancer, and is an important concern for Australians, particularly in Queensland, which has the highest incidence rates of skin cancer and mortality rates for malignant melanoma in the world [3]. Most skin cancers are preventable by encouraging consistent use of sun protection methods including using a broad spectrum water resistant sun protection factor (SPF) 30+ sunscreen, staying in shady areas, minimizing time in the sun between 10 am and 3 pm, and wearing a wide brimmed hat, sunglasses, and protective clothing to reduce sun exposure and sunburn [4]. Since sun protective behaviour depends on individual decision making processes, it is vital to understand people's attitudes toward, and motivations for, sun protection.

While previous research has focused on raising awareness and knowledge about the dangers of skin cancer and measuring the adoption of sun safe practices, there is little research aimed at understanding why people do or do not engage in sun protective behaviour [5]. International research indicates that the choice to use sun protection is likely to involve psychosocial factors such as attitudes, normative influences, and efficacy [6]; however, few studies have focused on understanding the psychosocial processes surrounding sun protection in an Australian context, with an associated absence of theory-based interventions.

In general, there is high awareness and knowledge about skin cancer risk in the community, and people's attitudes are fairly positive about performing sun protection [7]. However, these factors do not necessarily translate into attitudinally-consistent behaviour. The decision to use sun protection is complex, involving a range of situational and motivational factors. In particular, adolescents' sun safe behaviours may depend on the context of the situation where notable increased compliance to sun protect occurs in the school context [8], and are likely to be motivated by referent group norms (e.g., peer and friendship groups; [9]) and image norms disseminated by the media (e.g., perceptions of a tan as attractive; [10,11]). Furthermore, there is individual variation in the types of sun protection used and the frequency and adequacy of their use [5]. Specifically, adolescents have high levels of knowledge and awareness of the risks of skin cancer but engage in few sun protective behaviours [12], and have been reported to intentionally use a low SPF sunscreen or deliberately expose themselves to the sun to obtain a tan [7]. This deliberate exposure to the sun to obtain a tan is supported by more recent adolescent sun safety research which suggests having a strong desire for a tan is associated with delaying the use of and using no sun protection [13]. The lack of correspondence between attitudes and behaviour has long been a focus for social psychology with many researchers arguing that a focus on people's attitudes do not account for the range of influences that may potentially guide behaviour [14].

The Theory of Planned Behaviour [TPB; 15] is a model developed in response to identified inconsistencies between people's attitudes and actions (see Figure 1). The TPB is a well-validated model that has been used to explicate the attitude-behaviour relationship and accounts for the complexity of people's decision making. It specifies intentions as the most proximal determinant of behaviour with intentions being influenced by attitude (positive or negative evaluations of performing a behaviour), subjective norm (perceived social pressure to perform or not perform a behaviour), and perceived behavioural control (perceived ease or difficulty of performing a behaviour; also thought to be a direct predictor of behaviour; [15]). Attitude, subjective norm, and perceived behavioural control are informed by underlying behavioural (i.e., costs and benefits), normative (i.e., specific referents' (dis)approval), and control beliefs (e.g., barriers and facilitators), respectively, and it is these beliefs that can be used to design interventions [16]. According to the theory, other factors relevant to sun protection decisions, such as sun safety knowledge or perceptions of risk for skin cancer/damage, are not believed to influence intentions or behaviour directly but would instead be expected to inform underlying sun protection beliefs [15].

**Figure 1 F1:**
[figure not shown]
**The Theory of Planned Behavior **[15].

Support for the TPB has been demonstrated in several meta-analyses including Armitage and Conner's [17] study which found, across a range of social and health behaviours, that the model accounted for an average of 39% and 27% of the variance in intentions and behaviour respectively. The TPB constructs have been used successfully by several international researchers [6,10,11] and a smaller number of Australian researchers [9,18,19] to understand the motivations underlying sun protection-related behaviours. The results of these studies demonstrate that the TPB is a useful theoretical framework for examining the prediction of sun protective practices.

Despite support for the TPB, the normative component of the model, which reflects social pressure from significant others to perform the behaviour [15], has emerged consistently as the weakest predictor of sun protective intentions [6,19], a trend which concurs with previous meta-analytic research [17]. Researchers, drawing on social identity theory [20] and self-categorization theory perspectives [21] have advocated for a re-conceptualization of the normative component in the TPB to consider the influence of the expectations and actions of a specific, salient, reference group (i.e., group norms) on intentions and behaviour [19,22].

Group norms involve a consideration of whether important group members perform the behaviour (i.e. behavioural norm) and the evaluation of the behaviour by the group (i.e. group attitude). In the case of sun protection, for instance, people may be more likely to use sun protection if they believe that it is a usual and valued behaviour performed by other group members (e.g., friendship groups for adolescents). Terry and Hogg [19] found support for the positive effect of group norms (rather than subjective norms), in an extended TPB, on Australian female university students' intentions to sun protect. Similarly, White et al. [9] found a direct effect for group norms (in addition to subjective norms) on young Australians' sun protection intentions and behaviour.

Image norms are also another potential source of normative influence relevant to people's intentions and behaviour to sun protect [10]. For example, many adolescent females deliberately expose themselves to the sun with the sole purpose of developing a tan because a person with a tan is perceived as more attractive and healthy. Image norms reflect the self-presentational concerns of individuals about their image and are the cognitive representations of stereotypical members of particular groups (e.g., tanned people) [10]. Image norms are more distant from the individual than immediate referent norms (i.e., subjective or group norms) and are a general representation of the values of society as a whole (e.g., the media). Jackson and Aiken [11] focused on changing normative perceptions about the attractiveness of being tanned. They suggested that increasing the attractiveness of pale image norms may be effective in producing sun protective behavioural change [11].

Given the potential importance of social influences on adolescent sun protection decision making, it is important for researchers to consider targeting a range of different sources of social influence when developing programs to improve adolescent sun safe practices. In consideration of the useful contribution of group and image norms, within models such as the TPB, to predicting sun protection it seems warranted that these sources of social influence form a key focus of sun safety intervention programs.

Most sun safety interventions are educational in nature, designed to increase awareness and sun safety knowledge or perceptions of risk for skin cancer/damage [23]. While it is important to promote awareness about the effective use of sun protection, increasing people's knowledge and awareness of risk has not been shown to increase sun protection behaviour and there is a recognized need, both in Australia and internationally, for more novel interventions targeted at both adults and adolescents [23,24]. The belief basis of the TPB is useful in developing interventions to encourage behavioural change and may involve altering existing behavioural, normative, and control beliefs or exposing participants to new beliefs [16]. Hardemann et al. [25] reviewed 24 TPB intervention studies (21 of which were health related) and concluded that approximately half of the interventions were successful in changing intentions, with two-thirds successful in changing behaviour.

Two US-based interventions [11,26] have used some, but not all, components of the TPB to engender sun protection behaviour change. Mahler et al. [26] found that primarily female university students exposed to UV photo and photoaging stimuli who also received supportive information related to two types of norms (personal norms - what one 'should' do, and descriptive or behavioural norms about the sun protection behaviour of friends and peers) showed greater levels of self-reported sun protection behaviour than control participants over a 1-month period. The study focused on risk-related factors (susceptibility to a decline in health and appearance as a result of sun exposure). According to a TPB perspective, however, any risk-related factors would be reflected in the underlying costs (attitudes) and control perceptions. As Mahler et al.'s [26] study did not include a consideration of norms in the context of other known influences on sun safe behaviour such as attitudinal and control factors, it is not possible to determine the effects of these norms within the context of a comprehensive model of decision making.

Using appearance-based stimuli, Jackson and Aiken's [11] study of female university students' sun protection behaviour showed that, relative to the control group, the intervention increased participants' immediate perceptions of the benefits of sun protection, efficacy for sun protection, and image norms for being pale, as well as sun protection intentions with increases in intentions and behaviour at a 2-week follow-up. Although Jackson and Aiken [11] incorporated additional norms within the TPB, the original normative component of the model (i.e., subjective norm) was not included in the study, thus preventing a full comparison of the different sources of normative influence including the original conceptualization of norms proposed by Ajzen [15]. In addition, the generalisability of the findings of these two studies is limited by the focus on a single population (primarily female university students). Skin cancer rates in Australia are projected to increase more for men than women [1] and, adolescents, despite high levels of knowledge about the dangers of skin exposure to the sun, practice few sun protection behaviours [12]. Normative influences are especially salient for young people's health behaviour decision making [27], including their sun safe behaviours [9]. Thus, an assessment of the effectiveness of an intervention incorporating norms with a broader sample of respondents (e.g., males, adolescents) is particularly important.

The authors completed a pilot study [28] targeting the sun protection intentions and behaviours of young Queensland secondary school students (n = 80; 14.53 ± 0.69 years). Approximately half of the participants (n = 34) were exposed to the intervention with the other set of participants (n = 46) comprising a wait-list control group. The results revealed that students completing the intervention reported stronger sun-safe normative and motivator beliefs and intentions and the performance of more sun-safe behaviours across time than those in the control condition. However, while the results of the pilot intervention evidenced some positive changes in high school students' sun protection intentions and behaviour, the mechanism by which these changes occurred was unclear due to the limited number of participants providing follow-up data and the short follow-up time frame. Therefore, there is a need for refinement and replication of the intervention and evaluation of its components with a larger sample of participants. The present study builds on this successful pilot work to conduct a large-scale trial of this approach.

This paper presents the study protocol for a large-scale school-based intervention to improve sun protective behaviour in adolescents. The research will use an extended version of the TPB [15] to develop and test the utility of a sun protective intervention derived from this approach. The intervention will target previously identified costs and benefits, important referents, and barriers and motivators. We hypothesise that adolescents exposed to the intervention will report a significant improvement in their beliefs, intentions, and behaviour for sun safety from pre- to post-intervention compared to adolescents in the control group. We expect a significant improvement over time for all constructs, except for control belief barriers where a decrease is expected. This research will address a gap in the literature given the paucity of interventional sun safety research in Australian, and the results of this study will provide valuable new information about an intervention to improve sun protective behaviour in adolescents where timely strategies are required to develop lifelong sun protection habits.

